### Sample size

Sample sizes were calculated for both the primary outcomes to provide at least 80% power at the 5% significance level. Based on heat-related symptoms and illness prevalence of 28.9%^21^ and an estimated intracluster correlation coefficient (ICC) of 0.0122, we calculate that 11 clusters per arm (22 clusters in total) with 70 to 80 households per cluster are needed to detect a 30% relative difference in heat-related illnesses while allowing for a 10% attrition rate. We treat 28.9% as a conservative estimate given the longitudinal nature of the primary outcome, as cumulative prevalence over the surveillance period is expected to exceed this single-time point prevalence. To assess quality of life changes, we estimate that with 11 clusters per arm 60 households per cluster are required based on the variability in baseline WHO Quality of Life Brief tool (WHOQOL-BREF) scores reported in Lodhi *et al*,^22^ which documented an average score of 68 (18.0) to detect a difference of 4 points in quality of life score assuming an ICC of 0.015. As the heat-related illness outcome required the larger sample size, the final enrolment target was set at 70–80 households per cluster, which also provides adequate power for the quality-of-life outcome. To assess physiological heat strain, we calculated that a subsample of eight adults (aged 18 years to 60 years) per cluster (balanced by gender) would be required to detect a 15% change in average heart rate, among those who are exposed to heat stress assuming a baseline of 66±12 bpm,^23^ an ICC of 0.1736 and 90% power. Given the complexity of the assessment process, we anticipate a higher attrition rate in this subset and have inflated the sample size by 30% to 10 individuals.

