For binary outcomes, the ICC was derived from an assumed cluster-level prevalence variation of ±10%, with the coefficient of variation (CV) estimated from this range and the ICC subsequently calculated using the relationship ICC=k²×P/(1−P), where k is the assumed between-cluster CV of the prevalence, following Pagel *et al*.^24^ For continuous outcomes, the ICC was estimated as the ratio of between-cluster variance to total variance,^25^ with total variance sourced from reference studies and a minimum between-cluster difference of ±9 units assumed. Each co-primary outcome is independently powered at 80% or above. To control the family-wise type I error rate across the two co-primary outcomes, hypotheses will be tested using a prespecified fixed-sequence (hierarchical) procedure: heat-related illness will be tested first at the two-sided 0.05 level, and quality of life will be tested at 0.05 only if the first test is significant. As each outcome is independently powered, this procedure incurs no loss of power. Quality of life is assessed at three time points per year over 2 years; the cross-sectional calculation above is therefore conservative, as the planned repeated-measures mixed-effects analysis increases precision by combining information across visits.

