### Statistical analysis

The trial has two co-primary outcomes, heat-related illness and quality of life. These outcomes will be evaluated independently to assess the effectiveness of the intervention. All statistical analyses will be conducted using STATA V.18.0 (https://www.stata.com), following an intention-to-treat approach while accounting for the cluster-randomised trial design. Baseline characteristics will be analysed to assess comparability between intervention and control arms. Descriptive statistics will summarise household and participant characteristics, and any important imbalances at baseline will be adjusted for in the analysis. No interim analysis or formal stopping guidelines are planned given the low-risk nature of the intervention.

Statistical analyses will account for the cluster-randomised design by incorporating clustering through random effects or robust variance estimators, as appropriate. For outcomes measured repeatedly over time, within-participant correlation will be accommodated using repeated-measures mixed-effects models. Intervention assignment and seasonal variation will be included as fixed effects in all applicable models, while relevant baseline covariates and baseline outcome values (where available) will be adjusted for. Model assumptions, including overdispersion for count outcomes, will be assessed and alternative modelling approaches (eg, negative binomial models) will be used where appropriate. Missing data will be examined and handled using complete-case analyses or multiple imputations, depending on the extent and pattern of missingness. Sensitivity analyses will be performed to assess the robustness of findings to different assumptions regarding missing data.

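### The claim that the fixed sequence costs no power holds for heat-related illness but not for quality of life, whose power is the chance that both tests are significant

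*Protocol article*

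**What the plan says.** The Sample size section of the protocol article sizes the trial for two co-primary outcomes and aims for at least 80% power on both. It states that "Each co-primary outcome is independently powered at 80% or above". For multiplicity it prespecifies a fixed sequence. The illness outcome comes first, at a two-sided 5% level. For the second outcome the rule is a gate: "quality of life will be tested at 0.05 only if the first test is significant". From these two facts it concludes: "As each outcome is independently powered, this procedure incurs no loss of power". It also calls the QoL calculation conservative, because the repeated assessments over two years are left out of it.

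The Statistical analysis section names the same two co-primary outcomes and says "These outcomes will be evaluated independently to assess the effectiveness of the intervention". Neither that paragraph nor the primary outcome analysis that follows mentions the sequence.

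**The concern.** A fixed sequence avoids splitting alpha, and only the first hypothesis in it keeps its marginal power. The second is declared only if the first test and the second test both reject. Powering each outcome separately does not protect the second one: whenever heat-related illness misses significance, QoL cannot be declared, however strong its own result.

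At stake is how a missing QoL claim will be read. A reader who takes the sentence at face value will assume that the trial had at least an 80% chance of declaring the 4-point QoL difference if it was real. Under the plan's own rule and inputs that chance is lower over most of the plausible range. A secondary matter is that the Statistical analysis section leaves open how its wording on independent evaluation fits the gate.

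**Working it through.** **Inputs (Sample size section).** 11 clusters per arm; two-sided alpha 0.05. Heat illness: prevalence 28.9%, powered to "detect a 30% relative difference in heat-related illnesses" (0.289 against 0.289 × 0.7 = 0.2023), "estimated intracluster correlation coefficient (ICC) of 0.0122", 70–80 households per cluster, 10% attrition (70 becomes 63, 80 becomes 72). QoL: SD 18, difference 4 points, ICC 0.015, 60 households per cluster. Assumed here: one respondent per household, and a correlation ρ between the two test statistics, which the plan does not give.

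**Step 1: reproduce the marginal powers.** Effective n per arm = 11m / [1 + (m − 1) × ICC].

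- Heat illness, m = 63: 693 / 1.756 = 394.6. With mean proportion 0.24565, power = Φ{[0.0867 − 1.96 × √(0.3706/394.6)] / √(0.3669/394.6)} = Φ(0.873) = 80.9%. At m = 72 it is 83.6%, and at m = 80 it is 85.5%.
- QoL, m = 60: 660 / 1.885 = 350.1. Power = Φ[4 / (18 × √(2/350.1)) − 1.96] = Φ(0.980) = 83.7%. At m = 72 it is 86.8%, and at m = 80 it is 88.4%.

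The stated 80% or above is reproduced for both outcomes by the normal approximation.

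**Step 2: power through the gate.** P(QoL declared) = P(both tests significant). At ρ = 0 this is the product of the two powers; for ρ > 0 it comes from a bivariate normal. It can never exceed the smaller of the two powers.

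| Marginal power (heat illness / QoL) | ρ = 0 | ρ = 0.5 | ρ = 0.9 |
|---|---|---|---|
| 80% / 80% (the stated floor) | 64.0% | 68.7% | 75.0% |
| 80.9% / 83.7% (63 / 60 households) | 67.7% | 71.8% | 77.5% |
| 83.6% / 86.8% (72 / 72) | 72.6% | 76.0% | 80.9% |
| 85.5% / 88.4% (80 / 80, no attrition) | 75.6% | 78.6% | 83.0% |

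In every cell the gated power is below the QoL marginal power in the same row. The gap closes only as ρ approaches 1.

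**Step 3: small number of clusters.** With t tests on 20 degrees of freedom the marginal powers are 77.2% (heat illness, m = 63) and 79.9% (QoL, m = 60). Gated QoL power at ρ = 0 is then 61.6% (63/60), 66.7% (72/72) and 69.9% (80/80).

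**Step 4: does the repeated-measures margin remove the loss?** Suppose repeated assessments raise QoL marginal power to 95%. With heat illness at 80.9% and ρ = 0, gated power is 0.809 × 0.95 = 76.9%. With QoL power near 100% it equals heat-illness power, 81% to 86%. Precision on QoL helps, but the cap set by the first test stays.

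**The case against.** The sentence has a sound core. Because alpha is not split, both tests run at the full 0.05 and neither sample size needs the inflation that a Bonferroni division would require. For heat-related illness the claim is exactly right, and no number in the plan is wrong. This stands, but the sentence is not limited to the first outcome.

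The loss may also be smaller than the table shows. The plan regards 28.9% as conservative for cumulative prevalence, and heat illness is collected on all household members and analysed as episodes per person-week, while the calculation counts households. Household size is not given. Assuming 2 to 5 members, the plan's ICC and no extra correlation within households, heat-illness power would be about 92–97%. Gated QoL power at ρ = 0 would then be about 78% (0.917 × 0.846, 63 households, 2 members) to 84% (0.972 × 0.868, 72 households, 5 members). This is an optimistic bound, since correlation within households would lower it. It reduces the size of the problem without making the sentence true.

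Two stronger readings are tempting and are not supported:

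- A reader might infer that QoL power in this trial is 64%. That figure needs exactly 80% marginal power for each outcome and uncorrelated tests. The plan claims 80% or more, its inputs give more, and it states no correlation.
- A reader might infer that the Statistical analysis section contradicts the gate and loses family-wise error control, with error up to 1 − 0.95² = 9.75% for two independent tests. But "These outcomes will be evaluated independently to assess the effectiveness of the intervention" sets no alpha and no decision rule, and can simply mean separate models, which is what the primary outcome analysis goes on to describe. The Sample size section holds the only testing rule, and it is explicit and prespecified. The 9.75% arises only if analysts set that rule aside.

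**Conclusion.** The statement is correct for heat-related illness and wrong for QoL. Under the plan's inputs, with the normal approximation, one respondent per household and correlations of 0 to 0.5, QoL power through the gate is about 68–72% at 63/60 analysed households per cluster and 76–79% at 80/80. At the stated floor of 80% each it is 64–75% for correlations 0 to 0.9. Stronger correlation, greater heat-illness power than calculated or gains from repeated QoL measures would raise these figures; t tests on 20 degrees of freedom would lower them. In all cases heat-illness power is the ceiling. The fixed sequence itself controls the family-wise error, and the wording of the Statistical analysis section is an ambiguity to reconcile.

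**What to change.** In the Sample size section, limit the statement about power to heat-related illness. Add that QoL power under the fixed sequence is the probability that both tests are significant, and report it as a range with the assumed correlations and marginal powers beside it.

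In the Statistical analysis section, replace the wording on independent evaluation with, for example: the two outcomes are analysed in separate models and tested in the fixed sequence set out under Sample size.

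The cost is a few sentences and a less favourable stated power for QoL. The sample size, tests, order of testing and type I error control are unchanged.

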### Formative phase

The ReHAB intervention comprises two principal components: (1) community education and awareness and (2) structural modifications for heat adaptation (figure 1). The formative phase consisted of multiple activities designed to determine the specific intervention components which would be feasible, acceptable and cost-effective.

### Systematic review

A systematic review of community-based heat adaptation interventions in LMICs was undertaken.^26^ A total of 185 studies were reviewed to identify effective approaches and to highlight existing gaps in adaptation strategies. Findings from this review informed the development of a list of evidence-based interventions, which were subsequently used to guide discussions with communities, stakeholders and policymakers.

### Qualitative study

The second component of the formative phase involved in-depth interviews and focus group discussions with key stakeholders. These included policymakers, government officials across national, provincial and local levels, civil society representatives and community members, with particular emphasis on women. Insights from this work were used to assess potential educational and structural interventions, as well as appropriate delivery mechanisms. Detailed findings will be reported and published separately.

### Consultative workshops

A series of consultative workshops were conducted with a broad range of stakeholders, including municipal authorities, relevant government departments, technical experts and community representatives. These engagements were used to refine and finalise the intervention design.

### Pilot study

A pilot study was conducted in a single non-study village involving 20 households to assess participant recruitment, acceptability and feasibility of intervention, adherence to wearable devices and completeness of data collection procedures. The pilot was conducted from 10 April 2025 to 15 June 2025. During this phase, the complete set of intervention components were implemented alongside community engagement activities. Environmental data were collected to evaluate the effects on indoor and outdoor temperatures. Following completion, the findings were analysed and reviewed in collaboration with stakeholders and subject-matter experts to inform further refinement of the intervention.

### Intervention

#### Intervention arm: ReHAB

The ReHAB intervention was developed based on findings from the formative phase and comprises two components: (1) community education and awareness and (2) participatory structural modifications to support local heat adaptation. Behavioural interventions will be delivered through community mobilisation, while structural interventions will focus on modifying existing structures to reduce indoor temperatures. As the unit of randomisation is the cluster, so intervention delivery is standardised at the cluster level, with all intervention clusters receiving the same community education and mobilisation package and a proportional distribution of structural interventions.

##### Community education and awareness

The educational component of ReHAB was developed based on findings from the formative phase, including systematic review, qualitative work, stakeholder consultations and pilot testing. Community mobilisation will be implemented throughout the intervention. Community groups (CGs) will be established across all 11 intervention clusters, with separate male and female representation. Each CG (6–8 members) will include local government representatives, elders, religious leaders and male and female community members. CGs will lead mobilisation activities and support surveillance of the primary outcome (heat illness).

Activities will include dissemination of heatwave warnings, awareness sessions and door-to-door outreach on heat-health practices (hydration, clothing and activity scheduling). CGs will maintain logbooks to record healthcare visits within their catchment areas and attendance in community meetings. Practical demonstrations of cooling strategies (eg, shade setup, light clothing, wet towels, misting and work–rest–shade cycles) will be conducted, supported by Information, Education and Communication (IEC) materials. This structured, behaviour-focused delivery aims to ensure both the uptake and sustainability of protective cooling practices. Community hydration measures (eg, temporary drinking water facilities) will also be implemented to reduce dehydration among outdoor workers.

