### Control arm

The control arm will receive routine care and usual public-sector health services and general government or media heat-related information which is available to the wider population with no additional intervention. Selected community representatives will conduct surveillance for heat-related illnesses.

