Data on signs and symptoms of heat-related illness will be collected through multiple sources to minimise missed events during the study period in the intervention and control clusters. Suspected heat-related illness episodes identified through community surveillance, household surveys or health facility records will be classified according to the predefined symptom-based algorithm by study data collectors as presented in figure 2 and categorised using International Classification of Disease, 11th Revision and institutional criteria. Events that would be identified through community surveillance will be visited by data collectors who will use the same survey tool, and reported health facility visits will be verified through facility records, where feasible. Quality of life data will be obtained through repeated household surveys, with the selected index adult serving as the respondent (Table 3).

Quantitative data will be collected using handheld devices with a custom-built Java application, with MySQL and SQLite used for data storage. Built-in range checks, consistency checks and skip patterns will minimise data entry errors. Any discrepancies will be verified and resolved through follow-up with data collectors. Each participant will be assigned a unique identifier generated by the purpose-built Android application to maintain anonymity. All data will be securely stored behind firewalls and fully anonymised prior to analysis.

In the second year of intervention, 5 mL venous blood samples will be collected from participants in both intervention and control households during peak heat time. Samples will be obtained by trained phlebotomists using standard aseptic techniques and stored in a biobank according to established protocols. These samples may be used for future exploratory analysis of heat-related biomarkers which have not been specified yet.

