#### Primary outcome analysis

For each participant, a summary record will be constructed comprising the number of heat-related illness episodes and the number of assessment occasions (or person-time) over which the individual was observed. To assess the intervention effect, a Poisson regression model with cluster-level random intercepts will be used, accounting for intracluster correlation. The number of heat-related illness episodes/events will serve as the numerator, while person-weeks at risk will be used as the denominator. Results will be presented as incidence rate ratios (IRRs) with 95% CIs.

Duplicate reports identified across multiple sources will be flagged in the database using participant ID, household ID, date of onset, symptoms and care-seeking information to ensure that each event is counted only once. Symptoms or events continuing from a previous reporting period will be considered part of the same illness episode. A new episode will be defined as either the onset of symptoms following a symptom-free interval of at least 2 days after the previous episode or the occurrence of additional new symptoms in a participant with ongoing previously reported symptoms. For quality-of-life assessments, changes from year one to year two will be compared across three assessment points per year. Summer and winter quality-of-life scores will also be analysed separately. Results will be reported as adjusted mean differences with 95% CIs.

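### Case-finders for heat-related illness differ by arm and all report sources are pooled, so any arm difference in detection multiplies the primary IRR directly, in an unknown direction

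*Protocol article*

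**What the plan says.** Under Community education and awareness, community groups of 6–8 members are set up in all 11 intervention clusters. They run awareness sessions and door-to-door outreach, and "CGs will lead mobilisation activities and support surveillance of the primary outcome (heat illness". The Training section adds that they are trained in community-based surveillance of heat-related illness alongside prevention messaging. They also keep records: "CGs will maintain logbooks to record healthcare visits within their catchment areas".

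For the other arm, the Control arm section says: "Selected community representatives will conduct surveillance for heat-related illnesses".

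Table 3 schedules a weekly survey, facility data and community surveillance during peak summers for all members of included households. Under Household data collection, suspected episodes from any of these sources "will be classified according to the predefined symptom-based algorithm by study data collectors". Events found by community surveillance are visited and assessed with the same survey tool. Facility visits are verified where feasible. The Study design section states that participants and researchers cannot be blinded and that only the data analysis will be.

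Primary outcome analysis removes duplicate reports across sources and analyses episodes per person-week by Poisson regression, reported as an IRR. On continuing illness it says: "Symptoms or events continuing from a previous reporting period will be considered part of the same illness episode". A new episode begins after at least 2 symptom-free days, or with "the occurrence of additional new symptoms in a participant with ongoing previously reported symptoms".

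**The concern.** The people who look for cases between surveys are not the same kind of people in the two arms. In the intervention arm they deliver the intervention, are trained in surveillance and meet residents often. In the control arm they are representatives about whom the article says little else. The common survey tool and algorithm apply only once an event has been referred, so they do not equalise who is referred. Removing duplicates prevents double counting but does not equalise detection either.

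The outcome is symptom-based and includes mild conditions such as heat rash, cramps and fatigue, which need not reach a facility. The count can therefore depend on how closely someone asks, and the added-symptom rule strengthens that dependence.

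The stakes extend beyond one endpoint. Under Sample size, "heat-related illness will be tested first at the two-sided 0.05 level", and quality of life is tested only if that test is significant. A distortion of the heat-illness IRR also decides whether the second co-primary outcome is tested.

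**Working it through.** **Inputs from Sample size:** prevalence 28.9%; 30% relative reduction, so 0.289 × 0.70 = 0.2023; ICC 0.0122; 11 clusters per arm; 70–80 households per cluster; 10% attrition; and the aim "to provide at least 80% power at the 5% significance level".

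**Step 1. Reproduce the plan's figure.** The two-proportion formula gives 386 per arm before clustering. At 70 households less 10%, m = 63 and the design effect is 1 + 62 × 0.0122 = 1.756. Clusters needed: 386 × 1.756 / 63 = 10.76, so 11 per arm. The stated sample size reproduces and is not in question here.

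**Step 2. Effect of unequal detection.** Let r be the ratio of counted to true episodes in the intervention arm, divided by the same ratio in the control arm. Then observed IRR = true IRR × r. The documents give no value for r, so every value below is an assumption.

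Power was computed in two ways:
- Log-IRR scale, starting at exactly 80%: SE = |ln 0.70| / 2.80 = 0.127, and power = Φ(|ln(0.70 r)| / SE − 1.96).
- The plan's own design, 11 clusters of 67.5 retained households (75 less 10%), with a normal test or a t test on 20 df.

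| r (assumed) | Observed IRR if true IRR is 0.70 | Power, log scale | Power, plan's design (normal / t) |
|---|---|---|---|
| 1.0 | 0.70 | 80% | 82% / 79% |
| 1.1 | 0.77 | 54% | 59% / 55% |
| 1.2 | 0.84 | 28% | 32% / 30% |

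Worked case, r = 1.1: |ln 0.77| / 0.127 = 0.261 / 0.127 = 2.05, and Φ(2.05 − 1.96) is about 0.54.

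**Step 3. No true effect.** With true IRR 1 and r = 0.9, a significant result in favour of the intervention occurs in about 13% (log scale) or 14% (plan's design, t), against a nominal 2.5%. With r = 1.2, a false finding of harm occurs in about 40% (plan's design, t).

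**Step 4. What would produce such an r.** If a share s of counted events comes only through community surveillance, and that channel finds x times as many in the intervention arm, then r = 1 − s + s·x.
- s = 0.25, x = 1.2: r = 1.05, observed IRR 0.735.
- s = 0.50, x = 1.2: r = 1.10, observed IRR 0.77.
- s = 0.25, x = 0.7: r = 0.925, observed IRR 0.647.

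If s is small, r stays near 1.

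**Step 5. The added-symptom rule.** If a fraction q of illnesses is split into two episodes, r = (1 + q in the intervention arm) / (1 + q in the control arm).
- 20% in both arms: r = 1, no bias.
- 30% against 20%: r = 1.3 / 1.2 = 1.083, observed IRR 0.70 × 1.083 = 0.76.
- 40% against 20%: r = 1.4 / 1.2 = 1.167, observed IRR 0.82.

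**The case against.** The strongest reply is that most of the ascertainment is common to both arms: a weekly survey of all household members, facility data, some form of community surveillance, one tool and one predefined algorithm. Because duplicates are removed, community surveillance adds only what the survey misses. If that is little, r is close to 1 and the larger power losses do not arise. Several sources were chosen deliberately so that fewer events would be missed. All of this stands. It limits the likely size, but pooled sources with different case-finders still leave a route for r to differ from 1.

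Several stronger readings are tempting, but the article does not support them:

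- **That the groups run the case-finding.** They support one of three sources.
- **That control villages keep no logbooks.** The article is silent on this. In any case the logbooks record healthcare visits and meeting attendance and are not listed as a source of heat-illness events.
- **That the education teaches residents to recognise symptoms and so raises the count.** The outreach topics given as examples are hydration, clothing and activity scheduling. Better recognition is possible, but deliverers with a stake in success might equally report less.
- **That the two episode sentences contradict each other.** One can be read as covering symptoms carried over and the other as covering symptoms newly added.
- **That the damage cannot be repaired at analysis.** Flagging duplicates across sources suggests that reports can be traced to source, and an analysis by source could be specified in a plan not shown.

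**Conclusion.** The point holds as a design weakness, not as demonstrated bias. The text establishes three things: different case-finders by arm, pooling of all sources into the primary count, and symptom classification by data collectors whom I read as included in the statement that researchers are unblinded. It follows that any arm difference in detection passes in full into the IRR. Neither its direction nor its size can be derived from the documents.

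The figures show sensitivity and do not predict what this trial will find. They rest on an assumed r and on a standard error taken from a single-time-point prevalence calculation, not from the person-week rate that will be analysed. Under those assumptions, a 10–20% difference in detection is enough to turn an adequately powered comparison into one with about 54–59% or 28–32% power. A 10% deficit with no true effect raises the one-directional error from 2.5% to about 13–14%. The added-symptom rule matters only as an amplifier.

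**What to change.** 1. Define the primary count as episodes identified by the weekly survey scheduled in both arms, and state that study data collectors administer it identically in each. Put a source flag on every report from the start. Report the all-source count, with community surveillance and facility records added, as a prespecified sensitivity analysis.
2. Record only symptoms in the field, and apply the Figure 2 algorithm by program with arm masked.
3. Define a new episode only by the symptom-free interval of at least 2 days, and record the worst category reached within each episode.

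**Cost:** protocol and analysis-plan wording, a database field and a classification program, with no added visits or participants. Episodes seen only by other sources, including some facility-only and possibly severe events, leave the primary count, which is why the all-source analysis should be reported beside it. The change does not remove any effect of the education on what people report in the survey itself. That should be stated as a limitation.
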